### Primary outcome measure

The primary outcome is symptoms of GAD measured by the Structured Interview Guide for the Hamilton Anxiety Rating Scale (SIGH-A), at baseline and subsequent visits up to 18 weeks following randomization. The SIGH-A is a widely used measure of anxious symptomatology in GAD research. It includes measures of persistent worry, anxiety, mood, and somatic symptoms. The SIGH-A has been used in previous studies of pharmacological and psychological treatments for people with GAD. It is reliable (intraclass correlation coefficients for inter-rater reliability of 0.98 and test-retest reliability of 0.88), has high convergent validity with structured clinical ratings of symptoms of GAD (for example, MINI PLUS 6.0 [46]), and is sensitive to change [47, 48].

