### Statistical analyses

Analysis of data will be conducted with blinding to group allocations. The primary efficacy analysis will assess average treatment group differences for the primary outcome measure (SIGH-A) over the entire study period using a likelihood based mixed-effects model, repeated measures approach (MMRM). Results from the analysis of dichotomous data (for example, demographics and genetic data) will be presented as proportions (for example, relative risks), with 95 % confidence interval, and Fisher’s exact test *P* value where appropriate. Non-parametric statistics will be used when assumptions for parametric methods are violated. Cohen’s *d* effect sizes will be calculated. All tests of treatment effects will be conducted using a two-sided alpha level of 0.05 and 95 % confidence intervals. Data will be analysed using Statistical Package for Social Sciences software (SPSS) [55].

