### Power analysis

The study will recruit a sample size of 210 participants (105 participants per arm). The study is powered to detect a small-to-moderate difference between active treatment and placebo on efficacy outcomes. Data will be analysed using data with at least one post-baseline, and all data including baseline measurement, in an intention-to-treat analysis. As such, a conservative effect size F of 0.15 on the primary outcome measure (SIGH-A) for a two-tailed analysis (with alpha = 0.05), and the study powered at 80 % (Z beta = 0.80), with a correlation among repeated measures (analysis of variance (ANOVA) model) over six time points, will require 206 participants (critical F of 3.88). A sample size of 206 (rounded up to 210) will be sufficiently powered to provide a statistical difference between active treatment and placebo groups (using the intention-to-treat analysis) with the data.

The sample size of the imaging component of this study is 40 per treatment arm (*n* = 80). Following 12-week supplement administration, a recent MRS study with a sample size of 24 (12 in each arm) detected significant changes in metabolites by 39 % [60]. Our sample size of 40 participants in each arm will provide higher statistical power compared to previous studies, whilst still maintaining sufficient power with a 10 % participant attrition rate, as well as attrition due to unreliable metabolite estimates in one or both time points.

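### The primary SIGH-A contrast reads as an average over a period that includes baseline, which does not match the hypothesis of change after 16 weeks, and the role of baseline in the model is left unstated

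*Protocol article*

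**What the plan says.** Four parts of the protocol article bear on the role of baseline.

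- **Primary outcome measure:** SIGH-A is the primary outcome, measured "at baseline and subsequent visits up to 18 weeks following randomization".
- **Statistical analyses:** "The primary efficacy analysis will assess average treatment group differences for the primary outcome measure (SIGH-A) over the entire study period", by a likelihood-based MMRM. No model terms are listed.
- **Power analysis:** "Data will be analysed using data with at least one post-baseline, and all data including baseline measurement", under intention to treat. The calculation uses "a conservative effect size F of 0.15 on the primary outcome measure (SIGH-A") in a repeated-measures ANOVA "over six time points, will require 206 participants (critical F of 3.88"). A correlation among the repeated measures is mentioned, but no value is given.
- **Primary hypothesis:** superiority of kava is judged by change in SIGH-A after the 16-week treatment phase.

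The Study design section lists seven visits: week 0 and weeks 2, 4, 8, 12, 16 and 18.

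**The concern.** If the primary contrast is a plain group difference averaged over all SIGH-A measurements, week 0 is one of the values averaged. Randomisation makes the expected difference there zero, so the contrast shrinks by one sixth (six points, weeks 0 to 16) or one seventh (all seven visits). A raw average that includes the starting score is also not a measure of change: it mixes the starting point in instead of taking it out. The contrast therefore differs from the one the primary hypothesis names.

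The second matter is efficiency. Baseline SIGH-A is collected on everyone and would be expected to predict later scores. In an unadjusted average, part of any chance baseline difference passes into the estimate and adds to its variance. Adjustment removes that component at no cost in participants.

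**Working it through.** **Inputs.** From Power analysis: f = 0.15, so d = 2f = 0.30 for two equal groups; alpha 0.05 two-sided; 80% power; six time points; N = 206. Assumed, because not stated: compound symmetry with correlation r (0.3, 0.5 and 0.7 shown), a constant difference from week 2 onward, and no dropout. SD is set to 1.

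**Step 1: reproduce the stated sample size.** For a group main effect on the mean of m measures, the noncentrality is λ = N f² m / (1 + (m − 1) r), tested on F(1, N − 2). With m = 6 and r = 0.5, λ = 206 × 0.0225 × 6 / 3.5 = 7.95. Power is 80.1%, N = 206 is the smallest even total that reaches 80%, and the critical F(1, 204) is 3.887. With m = 6, correlations of 0.3, 0.4, 0.6 and 0.7 give 148, 178, 236 and 264 instead.

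**Step 2: identify the test.** A group-by-time interaction over six time points would have critical F(5, 1020) = 2.22. The stated 3.88 therefore belongs to a time-averaged group main effect, which agrees with the averaging described in Statistical analyses.

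**Step 3: compare three contrasts at N = 206, with d = 0.30 at each of weeks 2 to 16.** Here λ = (N/4) δ² / v, where δ is the contrast and v the variance of the per-person summary. The figures below take r = 0.5.

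- (a) Baseline is one of six averaged points: δ = 0.30 × 5/6 = 0.25; v = (1 + 5r)/6 = 0.583; λ = 51.5 × 0.0625 / 0.583 = 5.52.
- (b) Mean of the five post-baseline visits: δ = 0.30; v = (1 + 4r)/5 = 0.60; λ = 51.5 × 0.09 / 0.60 = 7.73.
- (c) As (b), adjusted for baseline: v = 0.60 − r² = 0.35; λ = 51.5 × 0.09 / 0.35 = 13.24.

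| Contrast | r = 0.3 | r = 0.5 | r = 0.7 |
|---|---|---|---|
| (a) baseline in the average | 79.0% | 64.7% | 54.1% |
| (b) post-baseline mean | 89.8% | 79.0% | 69.1% |
| (c) post-baseline mean, adjusted | 95.2% | 95.2% | 98.5% |

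At r = 0.5 the totals needed for 80% power are 296, 212 and 126. Averaging baseline in costs about 14 points (79.0 to 64.7%); not adjusting costs about 16 more (95.2 to 79.0%). If week 18 is also averaged with the effect kept, the three figures are 68.1%, 80.1% and 96.0%.

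**Step 4: chance imbalance.** At N = 206 the standard error of the baseline difference is √(4/206) = 0.139 SD. In contrast (a) at r = 0.5, the fraction passed on is (1 + 5r)/6 = 0.583. A one-standard-error imbalance therefore moves the estimate by 0.583 × 0.139 = 0.081 SD, about 27% of 0.30.

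**Step 5: readings under which 80% stands (r = 0.5).**

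- The six time points are weeks 2 to 18: the unadjusted post-baseline mean has 80.1% power, and 96.0% when adjusted.
- f = 0.15 already describes the average that includes baseline: the post-baseline difference is then 0.30 × 6/5 = 0.36. The planned test has 80.1% and the adjusted post-baseline mean 99.1%.

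**Step 6: a week-16 contrast.** If the hypothesis is taken as a single-visit comparison at week 16, adjusted for baseline, v = 1 − r². At r = 0.5, λ = 51.5 × 0.09 / 0.75 = 6.18 and power is 69.6%. At r = 0.3 and 0.7 it is 61.3% and 85.1%. The gain in (c) belongs to the averaged contrast and does not carry over to a single visit.

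**The case against.** The case against is substantial.

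- **No single sentence says that baseline is averaged.** The outcome section can be read as a measurement schedule. The Power analysis sentence can be read as describing which participants and data enter, which also fits baseline as a covariate or in a constrained response vector. The study period in Statistical analyses can mean follow-up. This stands as a reason for caution. The more natural joint reading still puts week 0 in the average, and nothing in the article excludes it.
- **Silence on covariates is not evidence.** A reader might infer that baseline is not adjusted for. The documents do not support that: the article gives the model in one sentence, and a covariate list is commonly left to the full protocol or SAP.
- **The six time points fit weeks 2 to 18 at least as well as weeks 0 to 16.** There are exactly six post-baseline visits. On that reading the power calculation contains no baseline value and shows no shortfall.
- **f = 0.15 is stated for the planned test.** If it already describes the diluted contrast, power is again 80.1% at correlation 0.5.
- **An unadjusted randomised comparison is valid.** A reader might call the carried-over imbalance a bias. It is not: it is random and already counted in the standard error, so it is a loss of precision.

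The team's previous GAD trial, described under Background evidence, reported a group-by-time interaction, which takes baseline as reference. That suggests this trial may intend the same, but the critical F of 3.88 is not that of a group-by-time test over six time points.

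**Conclusion.** The point holds as a defect of specification with a real efficiency cost. Taken together, the outcome, analysis and power sections describe a primary contrast averaged over a period that includes week 0. The hypothesis names change after 16 weeks, and the article does not say how baseline enters.

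It is tempting to conclude that the trial has 65% power instead of 80%. That holds only if week 0 is one of the six averaged points, d = 0.30 is the difference at each later visit, the correlation is 0.5, and the other assumptions above apply. Under either alternative in step 5 the stated 80% stands at that correlation.

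What does not depend on the choice of reading is the direction. At every correlation tried, the baseline-adjusted post-baseline mean has more power than the same mean unadjusted or the average with baseline in it. This is a free improvement and a needed clarification, not a demonstrated error in the stated power.

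**What to change.** In Statistical analyses, state that the primary MMRM contrast uses post-baseline SIGH-A values only, with arm, visit, arm-by-visit, baseline SIGH-A and baseline-by-visit as fixed effects. An equivalent form keeps baseline in the response vector with a common baseline mean across arms and takes the contrast over post-baseline visits.

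Name the visits in that contrast and make them agree with the primary hypothesis. If a single week-16 comparison is chosen, redo the power calculation for it (step 6); if a post-baseline average is chosen, reword the hypothesis to match.

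In Power analysis, reword the sentence on included data so that baseline is not an averaged outcome. Say which six visits are meant, give the assumed correlation, and say whether f = 0.15 refers to the post-baseline difference.

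The cost is a few sentences, with no extra data or visits. The article reports that recruitment has yet to start. Extra participants would be at issue only if a single-visit contrast is chosen and its recalculated power is judged too low.

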### Imaging analysis

#### Imaging data acquisition

A 3-tesla scanner (Siemens Tim Trio MR scanner) is utilised for the neuroimaging component of the study. *Structural MRI:* A high-resolution (1×1×1 mm) T1 weighted scan will be performed. *MRS:* To measure the level of metabolite concentrations within the region of interest (anterior cingulate cortex (ACC)), single voxel MRS will be applied. PRESS sequence (TE = 30, TR = 2000, Ave = 128, weak water suppression) is first conducted to measure the main metabolism, followed by MEGA-PRESS (TE = 68, TR = 2000, suppression frequency = 1.95 ppm, Ave = 64) [54, 56–58] sequence at the identical location to measure concentration of GABA. Finally a water-unsuppressed sequence (16 averages) will be conducted for quantification. *Functional MRI:* Resting state fMRI (EPI sequence, TE/TR = 30/2500, 3×3×3 mm, 33 slices, 10-min scan acquisitions) will be conducted with the subject’s eyes closed in addition to task-based cognitive activation fMRI study utilising IAPS to elicit anxiety (EPI sequence, TR = 2000, 3×3×3 mm, 27 mins).

#### Image data analysis

*MRS*: LC-model will be used to fit and quantify the concentration of all metabolites (total N-acetyl-l-aspartate, creatine, total choline, myo-inositol, glutamate/glutamine, and gamma-aminobutyric acid (GABA)), after quality control (that is, CLRB < 20 %, SNR >10). Further, partial volume effect will be corrected using high-resolution T1 structural image and in-house voxel co-registration script. Imaging data analysis will be conducted using Statistical Parametric Mapping (SPM) and MATLAB software [59]. *Functional MRI:* Pre-processing and statistical analysis will be conducted using SPM12 (Wellcome Department of Neurology) and associated toolboxes run on MATLAB [59]. Pre-processing will include slice timing correction, motion correction, co-registration of function and structural data, then non-linear warping into standardised stereotactic space (MNI) and spatial smoothing. Resting-state fMRI will be further band-pass filtered and de-trended, then subjected to correlational connectivity analysis using REST v1.8 (http://www.restfmri.net/forum/REST_V1.8). The pre-processed task-based fMRI data will be high-pass filter analysed using the general linear model approach in SPM12, from which contrast images of crucial interest will be generated and entered into second level group models. To test the longitudinal effect of treatment group, a flexible factorial design will be used with main effect of time and group, interaction of time × group and covariance. Significant clusters surviving multiple comparison corrections will be reported.

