#### Secondary hypotheses

2)Kava will be superior to placebo on a range of secondary affective disorder outcome scales (Beck Anxiety Inventory [39], Penn State Worry Questionnaire [40]*,* and Montgomery–Åsberg Depression Rating Scale [41]).3)Kava will be superior to placebo on health-related quality of life measured using The World Health Organization Quality of Life - BREF (WHOQOL-BREF) [42], the Social Re-adjustment Rating Scale [43], and the Kessler Psychological Distress Scale [44].4)Overall sexual satisfaction and performance rated on the Arizona Sexual Experiences Scale [45] will be in favour of kava compared to placebo, in women but not men.5)Personality trait factors including anxiety, extraversion, socialization, and aggression rated on the Swedish Universities Scales of Personalities (SSP) may be associated with GAD symptomatology and will be measured via this self-reporting measure.6)Anterior cingulate cortex (ACC) activation and metabolite profiles will be differentially affected in the kava treatment group over placebo from baseline to week 8. Specifically, for ACC metabolite levels, there will be an increase in GABA and decrease in glutamate/glutamine ratio (Glu/Gln); ACC activation: reduction in activation during resting state; ACC activation: reduction in activation associated with anticipatory anxiety in a task-dependent manner. Further, individual differences in rostral ACC activation measured pre-treatment may predict GAD treatment outcomes for kava compared to placebo. Increased levels of activity in the ACC will also be associated with better clinical outcome in GAD participants.7)Response to kava will be moderated by GABA transporter polymorphisms. Specifically, for every rs2601126-T allele or rs2697153-A allele an individual carries, the greater the reduction of anxiety that will be observed.8)Individuals in the kava group will have distinct gene expression change profiles compared to the placebo group. Specifically, we hypothesise that expression of GABA pathway genes will be up-regulated following kava treatment and remain stable in the placebo group.

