GRIK5	Glutamate receptor, ionotropic, kainate 5
GRIN1	Glutamate receptor, ionotropic, N-methyl D-aspartate 1
GRIN2A	Glutamate receptor, ionotropic, N-methyl D-aspartate 2A
GRIN2B	Glutamate receptor, ionotropic, N-methyl D-aspartate 2B
GRIN2C	Glutamate receptor, ionotropic, N-methyl D-aspartate 2C
GRM1	Glutamate receptor, metabotropic 1
GRM2	Glutamate receptor, metabotropic 2
GRM3	Glutamate receptor, metabotropic 3
GRM4	Glutamate receptor, metabotropic 4
GRM5	Glutamate receptor, metabotropic 5
GRM6	Glutamate receptor, metabotropic 6
GRM7	Glutamate receptor, metabotropic 7
GRM8	Glutamate receptor, metabotropic 8
ADRA1A	Adrenoceptor alpha 1A
ADRA1D	Adrenoceptor alpha 1D
ADRA2A	Adrenoceptor alpha 2A
ADRB2	Adrenoceptor beta 2
ADRB3	Adrenoceptor beta 3
SLC18A2	Vesicular monoamine transporter
SLC6A2	Norepinephrine transporter
CYP3A4	Cytochrome P450 3A4
CYP2D6	Cytochrome P450 2D6
CYP2E1	Cytochrome P450 2E1
AR	Androgen receptor
NRG1	Neuregulin-1
BDNF	Brain-derived neurotrophic factor
ABCG2	Breast cancer resistance protein
ABCB1	P-glycoprotein
GAPDH	Reference genes
SADH	Reference genes
B2M	Reference genesAnterior cingulate cortical (ACC) region metabolite profiles, including N-acetyl-l-aspartate (NAA), creatine (Crn), glutamate/glutamine (Glu/Gln), and gamma-amino butyric acid (GABA), will be measured using single voxel magnetic resonance spectroscopy (MRS) at weeks 1 and 8.ACC region activity at rest and functional connectivity network (that is, default mode network) will be analysed using resting-state functional magnetic resonance imaging (fMRI) at weeks 1 and 8.ACC region task-dependent activation levels associated with anticipatory anxiety will be assessed using task fMRI (the International Affective Picture System (IAPS; [52]) at weeks 1 and 8.Acute anxiety levels related to undergoing scanner session at weeks 1 and 8 will be measured on the Spielberger State-Trait Anxiety Inventory — Trait and State components [53].

Inclusion criteria*Aged between 18–70 yearsMeets the DSM-IV and DSM-5 diagnostic criteria for generalised anxiety disorder (GAD) based on structured interview; Mini International Neuropsychiatric Interview-6.0 (MINI 6.0) [54], (note that while the MINI 6.0 uses the DSM-IV criteria, the same criteria are used in the DSM-5)Presents with anxiety (SIGH-A ≥ 18) at the time of study entryFluent in spoken and written EnglishProvides a signed copy of the consent form

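### The one longitudinal imaging test named compares mean change between two scans; adjusting for the baseline scan is usually more precise, and offsets the planned 10% attrition if the between-scan correlation is below about 0.8

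*Protocol article*

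**What the plan says.** Hypothesis 6 (Secondary hypotheses) states that ACC activation and metabolites will be "differentially affected in the kava treatment group over placebo from baseline to week 8". The Secondary outcome measures section puts the imaging at two occasions: metabolite profiles "will be measured using single voxel magnetic resonance spectroscopy (MRS) at weeks 1 and 8", and resting-state and task fMRI at the same two weeks.

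The analysis is under Image data analysis. In the functional MRI text, after the second-level group models, the article says: "To test the longitudinal effect of treatment group, a flexible factorial design will be used with main effect of time and group", and then "interaction of time × group and covariance". It does not say what the covariance term is, and it does not mention adjustment for the first scan. For MRS, that section covers quantification, quality control, partial-volume correction and software, but names no comparison between arms.

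The Power analysis section says: "The sample size of the imaging component of this study is 40 per treatment arm". It describes this number as "whilst still maintaining sufficient power with a 10 % participant attrition rate". It then allows for a further loss whose size it does not give: "as well as attrition due to unreliable metabolite estimates in one or both time points". It gives no between-group effect size, standard deviation, power figure or between-scan correlation for imaging.

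**The concern.** With two scans per person, a time-by-group interaction is a comparison of change scores. A change score subtracts the whole baseline value, whatever the correlation between scans. When that correlation is modest, the subtraction adds noise. In a randomised comparison the baseline-adjusted week-8 difference estimates the same treatment effect, and the data determine how much of the baseline is removed.

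This matters because hypothesis 6 makes directional claims on several ACC measures from 40 people per arm. The Discussion says that imaging results will need correction for multiple comparisons and that the sample must be reached for adequate power. The choice of model can gain or lose as much as the allowed attrition, and the baseline scans are collected anyway.

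**Working it through.** **Inputs from the article.** 40 per arm with 10% attrition: 40 × 0.9 = 36 per arm, 72 in total. Two scans. Two-sided alpha 0.05.

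**Inputs assumed, because the article gives none.** The between-scan correlation r (range shown), equal variance at both scans (relaxed below), and a week-8 difference of 0.6 SD for the power illustration. The figure of 40 per arm cannot be reproduced, since no effect size, SD or power is stated for it.

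**Variances**, in units of the single-scan variance, per person:
- change score: 2(1 − r)
- baseline-adjusted week 8: 1 − r²
- ratio: (1 − r²) / [2(1 − r)] = (1 + r)/2

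**Against the planned attrition.** Going from 40 to 36 per arm lowers change-score power from 80.0% to 75.7%, for an effect that has 80% power at 40 per arm. With 36 per arm and baseline adjustment (large-sample):

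| r | variance ratio | equivalent change-score n per arm, 36/ratio | power |
|---|---|---|---|
| 0.3 | 0.65 | 55.4 | 90.9% |
| 0.5 | 0.75 | 48.0 | 86.6% |
| 0.7 | 0.85 | 42.4 | 82.2% |
| 0.8 | 0.90 | 40.0 | 80.0% |
| 0.9 | 0.95 | 37.9 | 77.8% |

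Break-even with 40 per arm requires (1 + r)/2 = 36/40 = 0.9, so r = 0.80. At r = 0.9 adjustment recovers 1.9 of the 4 lost per arm, about half.

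**Finite-sample cost.** Estimating the slope with 72 people multiplies the adjusted variance by 1 + 1/(72 − 4) = 69/68.
- Break-even with the 10% attrition: r = 1.8 × 68/69 − 1 = 0.774.
- Break-even with the change score itself: r = 2 × 68/69 − 1 = 0.971. Above that, adjustment is very slightly worse.

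A simulation with 36 per arm and 20,000 runs gave ratios of 0.667, 0.758, 0.914 and 0.960 at r = 0.3, 0.5, 0.8 and 0.9, and 1.006 at r = 0.98.

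**Larger total loss.** If a fraction L is lost in all, break-even is r = 1 − 2L: 0.7 for 15%, 0.6 for 20%, 0.4 for 30%. The article expects unquantified scan-quality losses beyond the 10%.

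**Unequal variances.** If s is the ratio of the week-8 SD to the baseline SD, the variance ratio is s²(1 − r²)/(1 + s² − 2rs). At s = 1.25 it is 0.89 at r = 0.5 (against 0.75 with equal variances) and 1.00 at r = 0.8 (against 0.90). The gain vanishes where the slope rs equals 1, as it does at 1.25 × 0.8. At s = 0.8 and r = 0.5 it is 0.57, so a smaller week-8 variance favours adjustment further.

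**Illustration at an assumed 0.6 SD**, 36 per arm, noncentral t, a single test at 0.05:

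| r | power, change score | power, adjusted | detectable effect at 80% power, change vs adjusted |
|---|---|---|---|
| 0.3 | 56.4% | 74.9% | 0.79 vs 0.64 SD |
| 0.5 | 70.9% | 82.6% | 0.67 vs 0.58 SD |
| 0.7 | 90.0% | 94.0% | 0.52 vs 0.48 SD |

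Paying for the slope lowers the adjusted powers to 74.3%, 82.1% and 93.7%.

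**The case against.** The strongest case against is that the sentence describes a voxel-wise model. It follows the second-level fMRI models and precedes the reporting of corrected clusters, and a flexible factorial is a reasonable tool there. The interaction is unbiased under randomisation, matches the baseline-to-week-8 wording of hypothesis 6, and concerns a secondary, mechanistic outcome. The primary efficacy analysis is untouched. All of this stands. It makes the point one of efficiency, but does not remove it: the ACC activation part of hypothesis 6 falls under this test, and no other longitudinal test is named.

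Four stronger readings are tempting, and the article does not support them:
- A reader might infer that adjustment always recovers the 10% attrition. That needs r below about 0.8, and no correlation is given.
- A reader might infer that the MRS metabolites are to be analysed by change score. No MRS group test is named, and a condensed article may leave that to a fuller document, so its absence is not a fault in itself. The scan-quality losses in Power analysis are MRS losses and should not be carried over to the fMRI model.
- A reader might infer that the model is certainly unadjusted. The undefined covariance term could mean covariates, so some adjustment cannot be excluded.
- A reader might infer that any baseline-adjusted model rescues people with one usable scan. Week-8 regression on baseline needs both scans unless a missing baseline is imputed. Only the mixed model keeps such people, and someone with only a baseline scan adds little to the treatment contrast.

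The 0.6 SD powers are also for one uncorrected test without further scan loss. They compare the two analyses and do not forecast the power of the planned imaging tests.

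**Conclusion.** The point holds as a conditional efficiency loss. The one longitudinal imaging test named is a change-score comparison, and adjustment for the baseline scan is not stated. With equal variances, adjustment cuts the variance by 35% at r = 0.3, 25% at 0.5, 15% at 0.7 and 5% at 0.9. That is equivalent to 54%, 33%, 18% and 5% more participants (1/0.65, 1/0.75, 1/0.85, 1/0.95). At 36 per arm the possible loss from adjusting is trivial and arises only above r of about 0.97. The gain can be smaller, or nil, if the week-8 variance exceeds the baseline variance.

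The conclusion assumes randomised arms with the first scan before treatment, which agrees with hypothesis 6 calling it baseline and pre-treatment, and a roughly linear relation between the two scans. Its size depends on a correlation that the article does not supply.

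**What to change.** For the hypothesis 6 ACC region-of-interest activation and resting values, define the treatment test as the week-8 difference between arms adjusted for the baseline value. Alternatively, use a mixed model for the two time points with one baseline mean common to both arms. The second has the same precision with complete data and also keeps participants with one usable scan, so it is the better choice if scans will be lost.

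Use the same model for MRS GABA and Glu/Gln. Keep the flexible factorial for the voxel-wise maps, and say what its covariance term contains. If baseline adjustment was intended there, one sentence settles it.

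The cost is a few lines of analysis text, one extra model on values taken from images already planned, and one degree of freedom for the slope. No further scans or participants are needed.
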